### Cost-effectiveness analysis

The cost-effectiveness analysis will assess the economic costs of each phase of the PBO LLIN, IRS, or LSM from both a provider and a societal perspective, using standard economic evaluation methodologies [91]. Economic costs will be estimated for all areas of resource use, regardless of whether they incur a financial expense [92]. For example, if IRS or larvicides have been donated or community volunteers are helping with the intervention free of charge, an economic cost will attach a market value to these resources. Economic costs will include initial setup investment (e.g., capital for vehicles used in transporting the insecticides; GPS units for house or habitat mapping; pumps, storage space, and equipment; and traps for mosquito surveillance), running costs (e.g., insecticides, salaries for field application staff, staff training, protective clothes, gloves, fuel costs, and vehicle insurance), and costs of program management and quality control (e.g., material procurement, project coordinator, and quality controller). The initial setup cost will be annuitized over each asset’s useful lifetime. This process reflects the value-in-use of a capital asset, not the cost when the item was purchased. We will record the number of person-hours used per month and the quantity of insecticides used to accomplish the intervention during the above experimental activities. Cost data on equipment and supplies will be obtained from local markets in Kenya and Ethiopia, labor costs from the MoH of Kenya and Ethiopia, and insecticide costs from the manufacturers. Costs will be measured in the currency in which the resources are paid, then converted to US dollars. This costing method includes costs involved in field intervention, quality control, and program evaluation. Costs associated with academic research will be excluded. Incremental cost-effectiveness ratios will be based on the primary endpoint (i.e., the economic cost per clinical malaria case prevented). One-way and multi-way sensitivity analysis will examine the cost-effectiveness implications of potential changes in labor cost, insecticide price, and insecticide application frequency and efficacy [93]. Costs and effects will be presented in both discounted and undiscounted form. Cost-effectiveness results will be compared among the two intervention groups and the control group, and among the four embedded adaptive interventions.

### Other related surveys

Similar bioassays or questionnaire surveys have been done by our group in different sites in western Kenya; details have been described in our previous studies [8, 94, 95]. Briefly, mosquito insecticide resistance surveys will be done twice a year to monitor if mosquitoes develop resistance to the newly introduced IRS and PBO LLIN interventions. Mosquito resistance to insecticides will be determined using standard WHO tube bioassays [8]. Insecticide decay will be tested using standard WHO cone test [94]. This will be done twice a year. The test will include both LLINs and IRS wall materials; details of the tests have been described in our previous study [94]. Questionnaire surveys on bed net ownership, net usage, and net physical integrity will be done once a year [95].

### Data analysis

Differences in clinical malaria incidence and vector abundance between the treatment and control groups will be analyzed using Poisson multivariate regression models with intervention, malaria risk, cluster, and calendar time as covariates, using a generalized estimating equation (GEE) approach with population at each cluster as an offset [96]. GEE is necessary because incidence will be modeled monthly as a longitudinal measure using grouped data. Intervention will be a time-varying covariate, since the treatment in a cluster may be adapted and readapted depending on the response to the previous treatment. The odds ratio and 95% confidence interval for clinical malaria rates between the treatment groups and the control group will be calculated. For the second aim analysis (estimation of outcomes for the 4 embedded adaptive interventions), weighted and replicated generalized estimating equations will be used to estimate the mean clinical malaria incidence rates among the 4 embedded adaptive interventions and to compare the slopes at each stage for each adaptive intervention. Here, weighting is necessary to account for the potential over- or underrepresentation of some groups (e.g., non-responders would have a 1/4 chance of following their assigned treatment sequence, whereas responders would have a 1/2 chance of following their assigned treatment sequence) [97, 98].

We will identify a final intervention strategy after all cost and effectiveness data are collected. The aim of this strategy will be to recommend an optimal intervention method given the local conditions at each site. For this purpose, we will adopt the *Q*-learning framework from the previous section on enhanced machine learning methods [99]. We will train a neural network to predict each method’s utility, accounting for both effectiveness (reduction in malaria incidence rate) and cost based on the conditions at each site, such as malaria risk and socioeconomic, entomological, and genetic features. All data collected throughout this research will be used to train the final model. To reduce model complexity, we will consider clustering sites into a small number of classes and then training a model to predict the efficacy of each method conditioned on each class. Once the *Q*-function is learned, we will identify the optimal intervention by choosing the intervention method that maximizes the learned *Q*-function.

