#### Sample size justification

The primary aim of this study is to determine which initial intervention, PBO LLIN or LLIN + IRS, is more effective in reducing malaria incidence after 36 months. The second aim is to estimate the mean outcomes of the 4 embedded adaptive interventions from months 16 to 36 and to identify the most effective intervention. Sample size calculation is based on the primary aim, using the primary outcome (clinical malaria incidence) and between-group comparison of the average clinical malaria incidence at month 36. The proposed sample size (*n* = 36 clusters) will detect a 10% reduction in clinical malaria incidence with 89.2% power using the current incidence rate in the study sites (302 clinic cases per 1000 person-years) and a 2-tailed *α* = 0.05 with a human population size of 500 per cluster (Table 3). If malaria incidence is 30% lower than the current value, the design will still detect a 20% incidence reduction with 97% power (Table 3). This calculation assumes a 1:1 response/non-response ratio, a fixed cluster size of 500 participants, and an intra-cluster correlation coefficient of 0.05 [89]. This sample size is likely powered to detect smaller changes in incidence reduction, as previous studies in Kenya and Ghana indicated intra-cluster correlation coefficients of < 0.02 [90].

**Table 3 Tab3:** Power calculation (%) for proposed cluster-randomized SMART trial. Shown are degrees of power to detect four levels of incidence reduction under three incidence scenarios

Annual incidence rate (cases/1000 population)	Reduction in malaria incidence			
	40%	30%	20%	10%
Observed in the site: 302	> 99.9	> 99.9	> 99.9	89.2
30% lower value: 211	> 99.9	99.8	97.0	59.0
30% higher value: 393	> 99.9	> 99.9	> 99.9	97.0

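### The only model left for the primary aim codes current treatment, so it does not estimate the randomised comparison of initial PBO LLIN with initial LLIN + IRS

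*Protocol article*

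**What the plan says.** The Sample size justification section states the aim: "The primary aim of this study is to determine which initial intervention, PBO LLIN or LLIN + IRS, is more effective", judged after 36 months. It bases the sample size on a "between-group comparison of the average clinical malaria incidence at month 36".

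The Data analysis section then describes two analyses.

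- The first is a GEE fit of "Poisson multivariate regression models with intervention, malaria risk, cluster, and calendar time as covariates". On coding it says: "Intervention will be a time-varying covariate, since the treatment in a cluster may be adapted and readapted depending on the response". Its output is a ratio with confidence interval for clinical malaria "rates between the treatment groups and the control group will be calculated".
- The other is introduced as follows: "For the second aim analysis (estimation of outcomes for the 4 embedded adaptive interventions), weighted and replicated generalized estimating equations will be used".

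The Stage 1 intervention section defines response by a cluster's reduction in malaria incidence relative to LLIN. The Stage 2 intervention section re-randomises non-responders only, while responders continue.

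**The concern.** A SMART answers the question of which initial intervention is better by keeping every cluster in the arm it was first randomised to, whatever stage 2 adds. That contrast includes the downstream consequences of the first choice, and randomisation protects it. A time-varying treatment code moves a cluster out of its initial group once it fails to respond. The coefficient for PBO LLIN then describes cluster-months while PBO LLIN alone is in use, and likewise for LLIN + IRS.

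There are two consequences. First, the estimand changes: any benefit or failure of the stage 2 options no longer counts towards the initial arm. Second, the switch depends on the cluster's own past outcome, so an unweighted comparison with control can mix treatment effect with selection. At stake is the trial's headline answer on which starting intervention to prefer. The cost-effectiveness comparison of the two intervention groups and control also uses the primary endpoint.

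**Working it through.** **Plan's own figure.** The documents give no number for this mismatch. The primary comparison carries a stated power of 89.2% for a 10% reduction. The usual design effect, 1 + 499 × 0.05 = 25.95, with 12 clusters of 500 per arm gives 10.7% instead. That is a separate matter, and nothing below depends on it.

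**Step 1: how much data changes label.**
- Inputs from the protocol: 36 clusters in three arms, so 12 per arm; 12 months of stage 1 follow-up and 18 of stage 2; a 1:1 response ratio.
- Cluster-months per initial arm: 12 × (12 + 18) = 360.
- Non-responders: 12 × 1/2 = 6. Relabelled cluster-months: 6 × 18 = 108, and 108/360 = 30%.
- At month 36, half of each initial arm sits under another code. What remains under PBO LLIN or LLIN + IRS is responders only.

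**Step 2: can the two estimands differ materially?** Assume that both initial interventions have rate ratio 0.9 against LLIN, that stage 2 options in the PBO path bring this to 0.5, and that those in the IRS path add nothing (0.9).
- Initial PBO arm, ignoring rate differences between responders and non-responders: [12 × 0.9 + 18 × (0.5 × 0.9 + 0.5 × 0.5)]/30 = (10.8 + 12.6)/30 = 0.78.
- Initial IRS arm: 0.90. Randomised PBO/IRS ratio: 0.78/0.90 = 0.87 over follow-up. In stage 2 alone, which includes month 36, it is 0.70/0.90 = 0.78.
- Current-treatment coding: every month under the PBO code has 0.9 and every month under the IRS code has 0.9, so the ratio is 1.00.
- Simulation (400 replicates, 500 people per cluster, 0.302 cases per person-year) gives 0.84-0.85 over follow-up for the randomised ratio and 1.00 for the time-varying model. The simulated value is below 0.87 because non-responding clusters have higher rates and so weigh more.

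**Step 3: selection bias with no true effect anywhere.** Assumptions not in the documents: between-cluster log-SD 0.25-0.4, cluster-by-period log-SD 0-0.2, block shifts of -0.4/0/+0.4 on the log rate, a 10% Ministry of Health threshold, and the response rule.

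| Model and response rule | PBO/LLIN and IRS/LLIN (truth 1.00) |
|---|---|
| Time-varying, no cluster effects, response judged by level | 0.87-0.93 |
| Time-varying, no cluster effects, response judged by change from baseline | about 1.00-1.02 |
| Time-varying, cluster fixed effects, five baseline months | 1.01-1.05 |
| Initial arm held fixed | 0.99-1.01 |

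For PBO/IRS, the time-varying model gives 0.99-1.01 when both arms switch alike. If the enhanced method assigned LLIN + IRS to PBO non-responders, it gives 0.96 without cluster effects and 1.06 with them.

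**Step 4: cluster in the covariate list, read as fixed effects.**
- An intercept, 35 cluster terms and 2 block terms make 38 columns of rank 36, so risk block is fully aliased.
- Without pre-intervention months, an intercept, 35 cluster terms, 6 treatment codes and 1 stage term make 43 columns of rank 41. The codes within the PBO path sum to that arm's cluster indicators, and the same holds for the IRS path. Neither PBO against LLIN nor PBO against IRS can then be estimated.
- With pre-intervention months coded as LLIN, the arm contrasts become estimable; the block aliasing remains.

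**The case against.** The Data analysis section does not call this model primary. Its treatment-against-control wording fits the purpose of stage 1, where current treatment and randomised arm are the same, and 70% of follow-up cluster-months keep their label. A PBO/IRS contrast can be formed from a multi-category term, and a condensed article need not name it. All of that is fair: the primary label is an inference by elimination, and the unnamed contrast is not itself the fault. But the time-varying coding is stated expressly for the period after adaptation, and a PBO/IRS contrast formed from it is still a current-treatment contrast.

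A reader might infer more than the documents support:

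- **That the head-to-head ratio is biased by response-driven switching.** With no true effect and similar switching in both arms, the selection largely cancels. The fault there is the wrong estimand.
- **That the treatment-against-control bias is certain and large.** It depends on a response rule that the protocol leaves open between level and change, and almost disappears under a change-from-baseline rule.
- **That the cluster term makes the bias worse.** With baseline months fitted, the bias reverses and is smaller. The sound objection is aliasing and non-estimability. It falls away if cluster means only the GEE grouping unit, a natural reading beside GEE.
- **That LSM or combination effects would be reported wrongly.** The embedded adaptive interventions already have a weighted-and-replicated GEE.

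**Conclusion.** The point holds as a mismatch between the stated primary question and the only model left to answer it, and it should be corrected before analysis. The mismatch follows from the Sample size justification and Data analysis sections alone. The 30% relabelling needs only the protocol's own 1:1 ratio. The contrast of about 0.84-0.85 with 1.00 illustrates how far the two estimands can part when stage 2 options differ in effect between paths; it rests on assumed effects and is not a forecast. Selection bias in the ratios against LLIN is possible but conditional, from almost none to about 0.87. The estimability problem applies only if cluster is fitted as fixed effects.

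**What to change.** For the primary aim, fit the Poisson GEE with the initial randomised intervention (LLIN, PBO LLIN, LLIN + IRS) as a fixed factor whatever the stage 2 assignment. Take risk block and calendar time as covariates, with baseline infection prevalence, already collected, if wanted. Use cluster as the GEE grouping unit only. Name the rate ratio of PBO LLIN to LLIN + IRS over one stated window as the primary contrast, and use the same window wherever the aim is described. Keep the weighted-and-replicated GEE for the four embedded adaptive interventions. Any model with time-varying current treatment should remain only as a labelled secondary analysis.

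The cost is analysis wording only: no change to randomisation, data collection or sample size.

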### Trial design and outcome measures

#### Initial cluster randomization

The SMART trial design includes two intervention stages (Fig. 2 and Table 1). Based on pre-intervention malaria risk analysis, study clusters will be stratified into three blocks with different risk levels as described above. In each block, clusters will be randomly assigned with equal probability to one of the three interventions in stage 1, i.e., LLIN, PBO LLIN, and LLIN + IRS (Fig. 2). Cluster randomization will be done using computer-generated random numbers. Ideally, each block will include 12 clusters and each of the three interventions will be assigned to four clusters in each block (Fig. 1).

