#### Stage 2 intervention

The stage 2 intervention will be 21 months long, including a 3-month intervention implementation and 18 months of follow-up on the interventions’ impact. The main objective of stage 2 is to identify the optimal adaptive intervention in clusters not responding to the stage 1 intervention, i.e., the non-response clusters at the end of stage 1 will receive a modified intervention to improve the outcome (reduction of malaria incidence) (Fig. 2). In particular, non-responders to stage 1 PBO LLIN treatment will be randomized with equal probability to either PBO LLIN + LSM (larval source management) or an intervention determined by an enhanced reinforcement learning method. Similarly, non-responders to stage 1 LLIN + IRS treatment will be randomized with equal probability to either LLIN + IRS + LSM or PBO LLIN + IRS. Therefore, this design has 4 embedded adaptive interventions (Table 2).

**Table 2 Tab2:** Four embedded adaptive interventions in the proposed SMART trial study

Embedded adaptive intervention	First-stage intervention	Status at end of first-stage treatment	Second-stage intervention option	Subgroup in the design
#1	PBO LLIN	Responder	Continue PBO LLIN	B + C
		Non-responder	PBO LLIN + LSM	
#2	PBO LLIN	Responder	Continue PBO LLIN	B + D
		Non-responder	Enhanced machine learning method	
#3	LLIN + IRS	Responder	Continue IRS	E + F
		Non-responder	LLIN + IRS + LSM	
#4	LLIN + IRS	Responder	Continue IRS	E + G
		Non-responder	PBO LLIN + IRS	

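### Unless a small-sample correction is specified, the planned GEE tests with 12 clusters per arm would run at about 7–10% rather than the nominal 5%

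*Protocol article*

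**What the plan says.** The Data analysis section of the protocol article assigns Poisson GEE on monthly grouped counts to the treatment-versus-control comparisons and promises 95% confidence intervals. For the second aim, "weighted and replicated generalized estimating equations will be used to estimate the mean clinical malaria incidence rates among the 4 embedded adaptive interventions". It does not say which variance estimator, small-sample correction or reference distribution will be used.

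The number of clusters is set elsewhere:

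- Initial cluster randomization: "Ideally, each block will include 12 clusters and each of the three interventions will be assigned to four clusters in each block".
- Stage 2 intervention: non-responders in each of the two active arms are split equally between two options.
- Sample size justification: "This calculation assumes a 1:1 response/non-response ratio, a fixed cluster size of 500 participants, and an intra-cluster correlation coefficient of 0.05".

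The last section also states what the tests are for. The primary aim compares PBO LLIN with LLIN + IRS. The second aim is to pick the best of four embedded adaptive interventions.

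On weighting, the Data analysis section gives as an example that "non-responders would have a 1/4 chance of following their assigned treatment sequence, whereas responders would have a 1/2 chance". The section on initial randomization says that "clusters will be randomly assigned with equal probability to one of the three interventions in stage 1".

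**The concern.** The sandwich variance used with GEE is justified when the number of independent clusters is large. With few clusters the residuals are too small on average, because the fitted means follow the data. The standard error is then biased downwards, and a normal reference ignores the uncertainty in that standard error. Both faults shorten confidence intervals and raise the false-positive rate.

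The independent unit here is the cluster, so 500 residents per cluster and monthly records do not help. The primary contrast has 12 against 12. Each embedded intervention is estimated from 9 clusters (6 responders and 3 non-responders), with the 3 non-responders given double weight.

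At stake are the choice between two initial interventions and the naming of a best adaptive strategy for a control programme. The cost-effectiveness comparison uses the same groups.

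**Working it through.** **Inputs**

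- Clusters per arm: 4 per block × 3 blocks = 12 (Initial cluster randomization).
- Clusters per stage 2 option: 12 × 1/2 non-responding × 1/2 randomized = 3 (Sample size justification; Stage 2 intervention).
- Nominal level: two-sided 0.05 (Sample size justification).
- Assumed, not in the document: between-cluster coefficient of variation 0.1, 0.25 or 0.5; equal cluster sizes; exactly 6 responders per arm; response independent of outcome.

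**The plan's own figure.** The article prints no check of the false-positive rate. Its nearest figure on the same counts is power: the design "will detect a 10% reduction in clinical malaria incidence with 89.2% power using the current incidence rate in the study sites", namely "302 clinic cases per 1000 person-years". With 12 × 500 = 6,000 people per arm and design effect 1 + 499 × 0.05 = 25.95, the effective size is 231.2 per arm. The standard error is √[(0.302 × 0.698 + 0.2718 × 0.7282)/231.2] = 0.0420, so z = 0.0302/0.0420 = 0.718. Power is Φ(0.718 − 1.96) = 10.7%, so 89.2% is not reproduced. That is a separate matter, and nothing below uses it.

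**Primary contrast, closed form.** For k against k cluster means, the uncorrected sandwich divides the sum of squares by k instead of k − 1. The test therefore rejects when |t| with 2k − 2 degrees of freedom exceeds 1.96 × √((k − 1)/k).

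- k = 12: the cut-off is 1.96 × √(11/12) = 1.877, and P(|t22| > 1.877) = 7.4%.
- Restoring k − 1 but keeping the normal reference: P(|t22| > 1.96) = 6.3%. Both parts of the correction are needed.

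**Primary contrast, simulation under the null** (Poisson GEE, independence working correlation, gamma cluster effects):

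| Setting | Rejection at nominal 5% |
|---|---|
| Arm terms only, 20,000 runs per setting | 7.4–7.8% |
| With block terms, 8,000 runs per setting | 8.2–9.5% |
| Degrees-of-freedom scaling and t reference | 5.0–6.3% |

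**Embedded interventions.** Each strategy has 6 responders with weight 2 and 3 non-responders with weight 4. The effective number of clusters is (12 + 12)²/(6 × 4 + 3 × 16) = 576/72 = 8. As a rough guide, the closed form at k = 8 gives P(|t14| > 1.96 × √(7/8)) = 8.8%. Simulation of the weighted and replicated GEE gave 8.4–10.0% for pairwise contrasts. A larger run (20,000 per setting) gave 9.6–10.0% for strategies from different initial arms and 9.2–9.8% for strategies within one arm.

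**Weights.** Unconditionally, responders have probability 1/3 and non-responders 1/3 × 1/2 = 1/6. Table 2 of the article starts all four embedded interventions in only two of the three arms. Given membership of those two arms (probability 2/3), the values are (1/3)/(2/3) = 1/2 and (1/6)/(2/3) = 1/4, as printed. Weights of 2 and 4 are proportional to 3 and 6. On the same simulated data both sets gave identical rejection rates (9.55%, 9.15% and 14.25% for the three tests compared).

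**The case against.** The strongest objection is that the article never says an uncorrected sandwich with a normal reference will be used. A correction and its degrees of freedom are details often left to an analysis plan, and that plan is not at hand. This stands as a limit. A reader might infer that the trial's confidence intervals are too short as a matter of fact, and the document does not support that. It does support a narrower statement: the article commits both aims to a large-sample method at cluster counts where the default version fails, and mentions no safeguard.

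A second objection is that the simulated model is simpler than the written one, which has a time-varying intervention, malaria risk, cluster and calendar time. The coefficients of variation are also assumed. Both are true. The closed form, however, gives 7.4% without any value for the coefficient of variation, provided cluster means are roughly normal with equal variance.

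Two stronger readings are tempting:

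- A reader might infer that 1/2 and 1/4 are wrong for a three-arm first stage. They are correct for the two arms that hold the embedded interventions, and no estimate, standard error or test changes. LLIN could be mis-weighted only if it entered the same model on a different scale, which the article does not propose.
- A reader might take 3 against 3 clusters as the relevant comparison, where the uncorrected test runs at 18.5%. That direct contrast is not the estimator the article names. A joint test of all four strategies would run at 14.7–16.2%, but the article does not state one.

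**Conclusion.** The point holds conditionally. With default GEE inference, nominal 5% tests would run at about 7–8% for the primary contrast, 8–9.5% with block terms, and about 8.5–10% for pairwise embedded-intervention contrasts, within or between initial arms.

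The arithmetic is firm for the primary contrast. The embedded-intervention figures rest more on the assumptions, above all that response is independent of outcome. Response is in fact defined from incidence. A systematic gap between responders and non-responders would enlarge the residuals around each strategy mean and could lower these rates, so they are not a bound for every setting.

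The shortfall is moderate, cheap to remove, and needs no change to design or data collection. If the analysis plan already specifies a suitable correction, the point is met.

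**What to change.** For the primary contrast and all embedded-intervention contrasts, state one of the following in advance:

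- a small-sample corrected sandwich variance (for example Kauermann-Carroll or Fay-Graubard) with a t reference on cluster-based degrees of freedom; or
- a permutation test that respects the blocks and, for embedded-intervention contrasts, the stage 2 randomization.

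The chosen version should be checked by simulation with the full written model, including settings where responders and non-responders differ, because corrections can be conservative with so few clusters.

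The cost is a software option, a sentence of text and wider intervals. For the primary contrast the factor is (2.074/1.960) × √(12/11) = 1.105, about 10% wider. With 8 effective clusters per strategy it is (2.145/1.960) × √(8/7) = 1.170, about 17% wider. Power falls accordingly.

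The weights need no change. A short note that the printed probabilities are conditional on the two arms in Table 2 is optional.
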